#### Exercise

The Active Australia Survey [59] is a validated questionnaire that measures physical activity behavior in adults, will be used to measure engagement in physical and sedentary activities (duration and nature); these behaviors are retrospectively reported by women for the past 7 days.

#### Food intake

A modified version of the valid [60] and reliable [61] National Nutrition Survey Food Frequency Questionnaire [62] will be used to assess food intake for the last 3 months.

#### Other relevant variables

Other variables will be included to ensure comprehensive assessment and will be examined as secondary, or covariate variables. These include parity, socioeconomic status, substance use, healthcare resource-use, perceived social support, coping style and appraisal of stressful events, beliefs about gestational weight gain, labor experiences (e.g., length, type), breast-feeding experiences, birth weight and delivery date.

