##### HC educational group sessions

In addition to the individual HC sessions, there will be 2 × 2 hour group education sessions that include the following key topics: dietary and physical activity guidelines in pregnancy; beliefs about pregnancy weight gain and body image; beliefs about postpartum weight loss and body image; mood changes during pregnancy; factors that protect a women against elevated depressive symptoms; and the negative consequence of postpartum weight retention for maternal and infant/child health. These group sessions will support behavior change processes begun in the initial individual session, and hence will incorporate HC; they will take place when women are 20 and 22 weeks gestation.

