### Economic evaluation

This study will include a formal economic evaluation to assess the cost-effectiveness of the intervention. The economic evaluation will comprise a cost-consequences analysis whereby the incremental costs of the intervention will be compared to the full spectrum of outcomes included in the study. This means that a series of cost-effectiveness ratios will be determined rather than just one - such an approach has been shown to be useful to decision-makers. The economic analysis will be primarily from the perspective of the health care sector. The intervention costs will be determined using standard financial records and interviews with project staff and financial officers. The evaluation will first measure and value any change to the use of health care resources over the period of the study between the two arms of the trial and then compare any additional costs to the additional outcomes achieved. Standardized economic evaluation techniques including incremental analysis of mean differences and bootstrapping to determine confidence intervals will be used in the evaluation.

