### Analyses

We will adhere to 'intention-to-treat' principles following CONSORT Statement guidelines to prevent introduction of systematic bias [48]. As such, baseline data will be secured prior to treatment allocation, missing values will be scrutinized to check for non-random distribution and primary analyses will be executed twice: once using observed data, and once using multiple imputation under multivariate normal assumptions using methods given by Schaffer [65], so that all participants will be analyzed in their allocated condition. Analyses of covariance (with "other relevant variables" from above as covariates) will test the between group differences in the primary and secondary outcomes at each assessment time point and across time points. The confounder-adjusted analysis of the proportion of women returning to pre-pregnancy weight at 12 months post birth in each group will be tested using a logistic regression model. The second hypothesis will be tested using hierarchical regressions and path analysis. In addition, to further clarify the direction of effects between two variables across multiple time points, cross-lagged panel analyses will be conducted, e.g., to determine whether the level of maternal activity/depressive symptoms is a cause or consequence of higher BMI. Finally, the interview transcripts will be analyzed using elements of phenomenology and thematic content analysis to determine barriers to adopting healthy behaviors for weight management and the support or resources that women find most useful in achieving their gestational weight gain/postpartum weight loss goals [25,66].

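### The between-group ANCOVA takes as covariates variables that arise after randomisation, so its estimate may not be the total effect of allocation

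*Protocol article*

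**What the plan says.** The Analyses section specifies the treatment comparison as follows: "Analyses of covariance (with 'other relevant variables' from above as covariates) will test the between group differences in the primary and secondary outcomes". The comparison is made "at each assessment time point and across time points".

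The covariate label points back to the section Other relevant variables. The list there begins with "parity, socioeconomic status, substance use, healthcare resource-use, perceived social support, coping style and appraisal of stressful events" and ends with "beliefs about gestational weight gain, labor experiences (e.g., length, type), breast-feeding experiences, birth weight and delivery date". The section says that these variables "will be examined as secondary, or covariate variables", but does not sort them between the two roles.

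Three other places fix the timing and the scope:

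- Participants: allocation follows the baseline assessment, which Table 1 puts at 14-16 weeks of gestation.
- Secondary outcomes: the measures described below that heading are taken at every assessment in Table 1, both before and after randomisation.
- Analyses: return to pre-pregnancy weight at 12 months is tested by a logistic model described as adjusted for confounders, none of which is named.

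The article describes no primary comparison that is unadjusted or adjusted for baseline values only. The two planned runs of the primary analyses, on observed and on imputed data, differ only in how missing values are handled.

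**The concern.** Covariates in a randomised comparison are safe when allocation cannot have influenced them. Two things can go wrong when it can. If the covariate lies on the path from intervention to BMI, adjustment removes the part of the effect that runs through it. If the covariate is a consequence of the intervention and shares unmeasured causes with BMI, adjustment opens a non-randomised path between arm and outcome (collider bias).

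The ANCOVA is the stated test for the primary outcome, maternal BMI, and for the secondary outcomes. The trial could therefore report, as its main result, a coefficient that does not answer the question in Specific aim 1: what being allocated to health coaching does to weight, compared with education alone.

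**Working it through.** **1. When can each covariate first be known, and does the article tie it to weight gain or to the intervention?**

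| Listed variable | Value possible before randomisation? | Link in the article |
|---|---|---|
| Labor (length, type) | No | Background: excessive gain is related to delivery complications and caesarean |
| Birth weight | No | Background: excessive gain is related to macrosomia |
| Breast-feeding | No | None stated |
| Date of delivery | No | None stated |
| Healthcare resource use | Yes; value to be used not stated | Economic evaluation will "measure and value any change to the use of health care resources over the period of the study between the two arms" |
| Beliefs about gain | Yes; value to be used not stated | Group-session topics include "beliefs about pregnancy weight gain and body image; beliefs about postpartum weight loss and body image" |
| Social support, coping, stress appraisal, substance use | Yes; value to be used not stated | None stated |
| Parity, socioeconomic status | Yes | None stated |

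Four variables are necessarily post-randomisation. For two of these, labor and birth weight, the article's own background gives a reason to expect a shift if the intervention reduces gain.

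**2. Can the rule be carried out at each time point?** At 32 weeks there is no labor, birth weight, breast-feeding or delivery date to enter. The covariate set as worded cannot be used for that comparison.

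**3. What does adjustment estimate?** The plan gives no figure on this point, so a simple linear model serves as illustration. Let T be the arm, M the post-randomisation covariate with within-arm variance 1, and U an unmeasured common cause with variance 1:

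- M = a·T + g·U + error
- Y = d·T + b·M + h·U + error
- Total effect of allocation: d + a·b
- Coefficient of T adjusted for M: d − a·g·h

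*Mediation only (g = h = 0).* The adjusted coefficient is (1 − share mediated) × total effect. With the article's target difference of 0.8 kg/m² and assumed shares:

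- 10%: 0.90 × 0.8 = 0.72
- 25%: 0.75 × 0.8 = 0.60
- 50%: 0.50 × 0.8 = 0.40

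*Collider only (b = 0, so d = −0.8), with g = 0.5 assumed:*

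- a = −0.3, h = 0.8: −0.8 + 0.12 = −0.68
- a = −0.5, h = 0.8: −0.8 + 0.20 = −0.60
- a = −0.3, h = −0.8: −0.8 − 0.12 = −0.92
- a = −0.5, h = −0.8: −0.8 − 0.20 = −1.00

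*No shift by treatment (a = 0).* The coefficient stays at −0.8.

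The bias can therefore go either way, and it vanishes if allocation does not move the covariate.

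**4. Does a power loss follow?** Inputs from the article: 110 per group, SD 2, α = 0.05 (taken as two-sided).

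- Unadjusted, for 0.8: SE = 2 × √(2/110) = 0.270, power 84%.
- SD held at 2 after adjustment: power for 0.72, 0.60 and 0.40 is 76%, 60% and 32%.
- M assumed to explain 25% of the within-arm BMI variance: the residual variance is 0.75 × 4 = 3 and b has size 1, so a has size 0.08, 0.20 or 0.40. SE = √(3 × (2/110) × (1 + a²/4)) = 0.234, 0.235 and 0.238. Power is 87%, 72% and 39%.

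The first of these last three exceeds the unadjusted 84%. No particular power figure follows from the document.

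**The case against.** The fairest defence is that the reference to the list is shorthand. The Analyses sentence does not say that all the variables enter every model, the list is described as serving in either of two roles, and a literal reading fails at 32 weeks. The authors may have meant a set to be chosen from the list, and a full protocol or analysis plan may settle it.

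Part of this stands: the article does not prove that every listed variable will be entered. But the Analyses section names the list as the covariates and makes no split. This is a stated rule, not an omitted detail, and as worded it admits four variables that cannot precede randomisation.

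A reader might infer more than the text supports:

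- *That resource use and beliefs about gain also arise only after randomisation.* Both can be recorded at baseline, and the Secondary outcomes schedule suggests that they may be. The defect for these is that nothing restricts them to the baseline value.
- *That the estimate will be biased.* This needs allocation to shift the covariate. The background supports that for labor and birth weight; nothing in the article shows it for breast-feeding or date of delivery.
- *That the intention-to-treat commitment is broken.* The article states it as analysing all women in their allocated condition, which adjustment does not breach. What changes is the quantity estimated.
- *That power falls by a known amount.* The results depend on an assumed mediated share and on how much BMI variance the covariate explains.
- *That the logistic model uses the same covariates.* It names none, so there is only a gap to close.

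**Conclusion.** The point holds, in this form: the covariate rule is wrong as written because it includes variables that can only be known after randomisation and leaves others open to follow-up values. The adjusted between-arm estimate may then not be the total effect of allocation. Neither the size nor the direction of any bias can be derived from the document. The 0.72 to 0.40 kg/m² range rests on an assumed 10% to 50% mediation of the 0.8 kg/m² target, and the −0.60 to −1.00 range on assumed collider parameters. The conclusion itself rests on neither; it follows from the timing of randomisation and the contents of the list.

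**What to change.** In the Analyses section, state that the covariates of all between-arm comparisons are limited to named values recorded before randomisation. Examples are baseline BMI, parity, socioeconomic status and, if wanted, baseline scores on the psychological scales. State the same limit for the logistic model and list its covariates.

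Use labor, breast-feeding, birth weight, date of delivery and follow-up values of resource use, beliefs, support, coping and substance use only in descriptive analyses or the Aim 2 mechanism analyses. Resource use also remains an outcome of the economic evaluation.

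The cost is about two sentences of wording. No measurement is added or dropped and the sample size is unaffected.

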### Economic evaluation

This study will include a formal economic evaluation to assess the cost-effectiveness of the intervention. The economic evaluation will comprise a cost-consequences analysis whereby the incremental costs of the intervention will be compared to the full spectrum of outcomes included in the study. This means that a series of cost-effectiveness ratios will be determined rather than just one - such an approach has been shown to be useful to decision-makers. The economic analysis will be primarily from the perspective of the health care sector. The intervention costs will be determined using standard financial records and interviews with project staff and financial officers. The evaluation will first measure and value any change to the use of health care resources over the period of the study between the two arms of the trial and then compare any additional costs to the additional outcomes achieved. Standardized economic evaluation techniques including incremental analysis of mean differences and bootstrapping to determine confidence intervals will be used in the evaluation.

### Qualitative interviews

We will invite 20 women (at 12 months post birth) from the HC Intervention and Education Alone groups (*n *= 40) to take part in an interview to obtain qualitative data in relation to barriers to adopting healthy behaviors for weight management and the support or resources that women found most useful in achieving their gestational weight gain/postpartum weight loss goals.

### Power, sample size, and retention

Given that the primary outcome of the study is maternal BMI, we aim to detect a clinically relevant difference in BMI of 0.8 kg/m^2 ^at 12 months postpartum. This difference is in accordance with the New Life (style) RCT that is currently being conducted in the Netherlands [63], that targets weight advice, weight development, nutrition and physical activity habits, but fails to target motivational variables, behavior-change assistance or psychological factors, such as depressive symptoms, anxiety symptoms, and body image. Consequently, the required *n *to detect this difference with 80% power at *α *= 0.05 and a standard deviation of 2 kg/m^2^, is 110 women per group; we have adopted this SD because we will also be measuring weight objectively at baseline and 12 months postpartum, removing any bias associated with self-report. Allowing for attrition of 20%, we will recruit 264 women and randomly assign 132 women into the HC Intervention and 132 women into the Education Alone control group. Our estimate of a drop-out rate is conservative and based on our previous large longitudinal studies with pregnant women and multiple time points [21,23,64]. As in our previous longitudinal pregnancy studies, this attrition rate of 20% takes into consideration that 5-7% of women may be diagnosed with gestational diabetes, which we expect to occur at 24-26 weeks; these women will therefore not affect the intervention, because we will over sample. A permuted blocks randomized treatment allocation schedule, produced by computer algorithm, will be used for the randomization process. To facilitate retention, we will build rapport with the participants through a study website, a regular newsletter, telephone support and advanced notification of assessments.

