## Discussion

With approximately 50% of Australian adult women of childbearing age being overweight or obese [67], the impact of pregnancy on women's weight status cannot be ignored [37]. Despite the puerperal period being a time of increased risk for both mother and child, it is also a time of unique opportunity, since pregnant women have frequent interactions with the health care system and may be especially receptive to behavior change recommendations, as evidenced by campaigns for smoking cessation in pregnancy [20]. Promoting healthy weight management around a given pregnancy is likely to favorably influence a woman's health entering her succeeding pregnancies, thus improving the health of not only her index pregnancy, but also subsequent children [68].

Our study responds to the urgent need to design effective interventions in pregnancy to prevent excessive gestational weight gain and postpartum weight retention [69]. To date, no intervention has been published that has targeted behavioral changes in relation to eating and physical activity as well as changes in psychological factors such as motivation, confidence, mood, and body image concerns, with the aim of preventing excessive gestational weight gain and 12-month postpartum weight retention. Our pregnancy HC Intervention is, therefore, novel and innovative. Moreover, it is unique in its application of health coaching principles and strategies to the life stage of pregnancy, that have been successful in instigating behavioral changes, in relation to chronic diseases including obesity, at other life stages. Our HC Intervention has been designed to be easily adopted by health professionals who work with pregnant women, such as obstetricians, midwives, GPs, and health psychologists. We additionally hypothesize that this intervention will provide a cost-effective approach to prevention of excessive gestational weight gain.

We expect the information obtained from this trial will be used to inform gestational and postpartum health practices and develop public health policies in relation to the prevention of excessive weight gain in pregnancy and weight retention post birth.

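### The BMI SD of 2 kg/m² behind the sample size is credible only as a residual or change SD, and the listed ANCOVA covariates do not name starting BMI

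*Protocol article*

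**What the plan says.** - **Power, sample size, and retention.** The calculation opens with "Given that the primary outcome of the study is maternal BMI" and continues "we aim to detect a clinically relevant difference in BMI of 0.8 kg/m^2 ^at 12 months postpartum". With 80% power, α of 0.05 and an SD of 2 kg/m², the article arrives at 110 women per group. The reason for the SD is "we have adopted this SD because we will also be measuring weight objectively at baseline and 12 months postpartum", which is said to eliminate self-report bias. The SD is not described as that of a change score or of a regression residual.
- **Participants.** Any BMI above 18.5 is eligible. No upper limit is given. Randomisation follows the baseline assessment.
- **Discussion.** The background population is described as "approximately 50% of Australian adult women of childbearing age being overweight or obese".
- **Analyses.** "Analyses of covariance (with 'other relevant variables' from above as covariates) will test the between group differences" in primary and secondary outcomes, at each assessment and across assessments.
- **Other relevant variables.** "These include parity, socioeconomic status, substance use, healthcare resource-use, perceived social support", followed by coping and stress appraisal, beliefs about weight gain, labour, breast-feeding, birth weight and delivery date. No BMI or weight of the mother is named.
- **Measures.** Pre-pregnancy BMI (from self-reported weight) and measured BMI are both collected at 14-16 weeks.

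**The concern.** The sample size rests on one SD, and the reason given for it does not bear on its size. The spread of BMI among women recruited across the normal, overweight and obese range is mostly real variation between women, and accurate scales do not shrink it. What could bring the SD down to about 2 is use of each woman's own starting BMI, as a covariate or by subtraction. The article does not say that the SD is of that kind, and the covariates it points to do not include the variable that would make it so.

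If the 12-month comparison were run with only the named covariates, it would face most of the between-woman variance, and a true benefit of 0.8 kg/m² would more likely be missed than found over most of the plausible range of SDs. Any chance imbalance in starting BMI would also pass into the estimate unadjusted.

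**Working it through.** **Inputs.** From the article: difference 0.8 kg/m², SD 2 kg/m², α 0.05 (taken as two-sided, since sidedness is not stated), power 80%, 110 per group. The article gives no cross-sectional BMI SD, so raw SDs of 3 to 6 are **assumed** as a range.

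**1. The plan's own figure.** n per group = 2 × (1.960 + 0.842)² × SD² / d² = 2 × 7.85 × 4 / 0.64 ≈ 98.1, so 99. The stated 110 is not reproduced but is on the safe side. With SE = SD × √(2/110) = 0.1348 × SD and power = Φ(0.8/SE − 1.96), SD 2 gives Φ(2.967 − 1.96) = 84%.

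**2. Can 2 be the raw SD?** If about half of women are at or above 25, the median is near 25. With a normal distribution and SD 2:
- 95% of women lie within 25 ± 3.9, that is 21.1 to 28.9.
- P(BMI ≥ 30) = 1 − Φ(5/2) = 0.6%, or about 2 of 264 women.

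Working backwards with **assumed** obese fractions of 10%, 15% and 20%, SD = 5/z gives 3.9, 4.8 and 5.9 (lognormal: 3.6, 4.5 and 5.6). An SD near 2 is not mathematically impossible. Placing half the women at 24.9 and the rest at exactly 25 or 30 gives 1.5 to 2.0 for obese fractions of 10% to 20%. But that needs everyone piled on the class boundaries.

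**3. Power at 110 per group if starting BMI is not used.** The 30% explained by the listed covariates is an assumption. It multiplies the SD by √0.7 = 0.837.

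| Assumed raw SD | Power, unadjusted | Power, 30% of variance explained | n per group for 80%, unadjusted | Variance the covariates must explain for a residual SD of 2 |
|---|---|---|---|---|
| 3 | 51% | 66% | 221 | 56% |
| 4 | 32% | 43% | 393 | 75% |
| 5 | 22% | 29% | 614 | 84% |
| 6 | 17% | 22% | 883 | 89% |

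Example, SD 5: SE = 0.674, 0.8/0.674 = 1.187, Φ(1.187 − 1.96) = 22%. The last column is 1 − (2/SD)².

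With the 132 per group that the power section randomises and 20% attrition, 132 × 0.8 = 105.6 remain. At 106 the unadjusted powers are 49%, 31%, 21% and 16%, so the picture does not change.

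**4. What an SD of 2 implies if starting BMI is used.** Residual SD = SD × √(1 − ρ²). Setting this to 2 gives ρ = √(1 − (2/SD)²) = 0.87, 0.92 and 0.94 for raw SDs of 4, 5 and 6. For a change score, SD × √(2(1 − ρ)) = 2 gives ρ = 0.875, 0.92 and 0.944.

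**5. Sensitivity to that correlation.** Power at 110 per group with starting BMI as covariate:

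| Raw SD | ρ = 0.85 | ρ = 0.90 | ρ = 0.95 |
|---|---|---|---|
| 4 | 80% | 93% | 99.7% |
| 5 | 62% | 78% | 97% |
| 6 | 47% | 62% | 89% |

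**The case against.** The strongest reply is that the article never says starting BMI will be left out. The covariate list is introduced as open-ended, the article condenses a fuller plan, and the exact model is commonly settled there. The analysis section also plans comparisons across time points. Researcher-measured BMI exists only at 14-16 weeks and 12 months, so such an analysis would draw on each woman's baseline value. The mention of weighing at both visits in the reason for the SD fits a change or within-woman SD. With a raw SD of 5 and correlation 0.92, a change score has SD 5 × √0.16 = 2.0, so the SD and one of the planned analyses may already agree.

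Much of this stands. A reader might infer that the planned analysis is known to have far less than 80% power. The documents do not support that: the list is not closed, no raw SD is given, and the unadjusted figures give the listed covariates no credit. The 50% figure also describes Australian women generally rather than this sample. A reader might likewise infer that randomisation ignores BMI, but the article is only silent on stratification.

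The reply does not rescue the text as it stands. The power statement concerns the 12-month difference, no change score is defined, the covariates are fixed by reference to a list without starting BMI, and the reason given for the SD is wrong under any reading.

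**Conclusion.** The point holds in a conditional form. As the between-woman SD of 12-month BMI in this population, 2 kg/m² is not credible. It can stand as a residual SD given starting BMI or as a change-score SD, and objective weighing justifies neither. The named covariates do not include starting BMI.

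If it is in fact omitted, power falls from 84% to between about 51% and 17% unadjusted over assumed raw SDs of 3 to 6, or 66% to 22% if the listed covariates explain 30% of the variance. These figures rest on the assumed SD range, a two-sided test and 110 women analysed per group. If starting BMI is used and its correlation with 12-month BMI is about 0.87 to 0.94, the stated SD is about right for raw SDs of 4 to 6.

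The firm finding is a mislabelled and wrongly justified SD, together with an unnamed key covariate. A loss of power follows only if that covariate is left out.

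**What to change.** - In **Analyses**, name measured 14-16-week BMI (and/or pre-pregnancy BMI) as a covariate in the primary model for 12-month BMI. One of the two may be enough, since they overlap.
- In **Power, sample size, and retention**, restate 2 kg/m² as the residual SD given that covariate, and state the raw SD and correlation it assumes (about 0.87 to 0.94 for raw SDs of 4 to 6), with a source.
- Delete the objective-measurement justification for the SD.

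The cost is wording only. Both BMI values are already collected before randomisation, and no visit or measurement is added. If the required correlation cannot be supported, the sample size needs to be recalculated. Adjustment also protects the estimate against chance imbalance in starting BMI, whether or not allocation is stratified.

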### Participants

Participants will be 220 pregnant women. Women will be able to participate if they provide informed consent, have a BMI > 18.5 (US IOM cut-off for normal weight), are 18 years of age or older, English speaking and less than 18 weeks gestation at recruitment with no history of disordered eating or diabetes. After baseline assessment, women who meet the eligibility criteria will be randomly allocated to either the HC Intervention group (*n *= 110) or the Education Alone group (*n *= 110). A coded, double-blinded, variable-length permuted blocks randomized treatment allocation schedule, produced by computer algorithm, will be used.

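### The sample-size figures do not follow from their inputs: 80% power needs about 99–100 evaluable women per group, not 110, and 132 per group leaves about 105 after 20% loss

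*Protocol article*

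**What the plan says.** All the inputs and outputs stand in one paragraph of the Protocol article, under Power, sample size, and retention. The target is a "clinically relevant difference in BMI of 0.8 kg/m^2 ^at 12 months postpartum". The remaining inputs are "80% power at *α *= 0.05" and "a standard deviation of 2 kg/m^2^, is 110 women per group". Sidedness is not given. The attrition step follows: "Allowing for attrition of 20%, we will recruit 264 women", after which the plan will "randomly assign 132 women into the HC Intervention and 132 women into the Education Alone control group". The paragraph names no design effect, multiplicity correction or other allowance between the inputs and the 110.

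Three other places give a different enrolment. The Participants section says "Participants will be 220 pregnant women" and allocates 110 to each group after baseline assessment. The Abstract (Methods/Design) also gives 220 women, and Table 1 heads both columns with n = 110.

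**The concern.** Two stated results look wrong against the plan's own inputs. The first is the requirement of 110 per group, which is higher than a standard two-mean calculation gives. The second is the recruitment target: 132 is exactly 110 × 1.2, and adding 20% to a number does not protect it against losing 20%. This is the only power justification in the article, and it supports the named primary outcome. At stake is whether a reader can trace how many evaluable women the trial needs and expects, and whether the 110 means women randomised or women evaluable. That distinction matters because other sections use 110 as the number allocated.

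**Working it through.** **Inputs** (Power, sample size, and retention): difference δ = 0.8 kg/m²; SD σ = 2 kg/m²; power 80%; α = 0.05; 1:1 allocation; attrition 20%. Assumption: two-sided test.

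**1. Reproducing the required number.** Normal approximation: n per group = 2(z₁₋α/₂ + z₁₋β)² σ²/δ².

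- Two-sided: 2 × (1.960 + 0.842)² × 4/0.64 = 98.1, so 99.
- Exact (noncentral) t-test: 100. At 99 per group its power is 79.97%, just short of 80%.
- One-sided: 2 × (1.645 + 0.842)² × 4/0.64 ≈ 77.3, so 78.

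None of these gives 110. At 80% power, two-sided, 110 per group would need an SD of about 2.12 or a difference of about 0.76. Changing the power does not reproduce it either: two-sided 85% power gives 113 and one-sided 90% power gives 108. An unstated 10% allowance would fit (99/0.9 = 110), but the plan does not mention one and applies its 20% attrition afterwards as a separate step. The covariate adjustment in the Analyses section would normally lower the number, not raise it.

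**2. Reproducing the recruitment target.** 110 × 1.2 = 132 and 220 × 1.2 = 264, which are exactly the plan's figures. To keep n evaluable after a fraction d is lost, the number to randomise is n/(1 − d):

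- Evaluable from 132: 132 × 0.8 = 105.6 per group, about 211 in total.
- To keep 110: 110/0.8 = 137.5, so 138 per group (276 in total; 220/0.8 = 275 if not rounded by arm).
- To keep 99 or 100: 99/0.8 = 123.75 and 100/0.8 = 125, so 124–125 per group (248–250 in total).
- Largest loss at which 132 still leaves 110: 1 − 110/132 = 16.7%.

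This step needs no assumption about the test or its sidedness.

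**3. Power at the numbers in play.** Two-sided, δ = 0.8, σ = 2; normal approximation: Φ(δ/(σ√(2/n)) − 1.960).

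| Evaluable per group | Where it comes from | Power, normal | Power, exact t |
|---|---|---|---|
| 110 | plan's required number | 84.3% | 84.0% |
| 105 | 264 randomised, 20% lost | 82.6% | 82.2% |
| 100 | exact t requirement | 80.7% | 80.4% |
| 99 | normal-approximation requirement | 80.4% | 79.97% |
| 88 | 220 randomised, 20% lost (110 × 0.8) | 75.6% | 75.1% |

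**The case against.** The strongest reply is that nothing is lost. The 110 errs on the high side, the attrition step falls short by only four or five women per group, and the remaining 105 still exceed the 99–100 needed. The plan also calls its drop-out estimate conservative, and 132 would leave 110 if loss stayed at or below 16.7%. The power goal itself is stated plainly as 80%. On this view the matter is a reporting correction.

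Much of that stands. A reader might infer from the faulty attrition step that the trial is underpowered, or that it must enrol 276. The documents do not support either inference: with 264 randomised and 20% lost, the plan's own inputs give about 82%.

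The reply depends, however, on 264 being the number randomised. Three other places in the article say 220, so the reassurance cannot be given without a condition. The opposite inference, that power is certainly about 75%, is not supported either. The power section is explicit about 264, and the 220 elsewhere could be the evaluable number carried over. The article does not settle which.

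The planned multiple imputation does not answer the attrition point. It keeps all randomised women in the analysis but does not restore the information lost with their outcomes.

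**Conclusion.** The concern holds as an arithmetic and reporting fault. On the stated inputs, with two-sidedness assumed, the requirement is 99–100 evaluable women per group. The stated 110 is about 10% too high for 80% power and corresponds to about 84%. Independently of that assumption, 132 per group with 20% loss leaves about 105, so the recruitment target does not deliver the number that the same paragraph calls required.

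The two errors offset. If 264 are randomised, expected power is about 82% and the stated 80% is met. If 220 are randomised, as the Abstract, Participants section and Table 1 have it, about 88 per group remain and power is about 75%, so the stated 80% would no longer hold. The sample-size arithmetic therefore matters mainly through the unresolved choice between 264 and 220.

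**What to change.** In the power section:

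- State the sidedness and the method. Give the requirement as 99 (normal approximation) or 100 (exact t-test) evaluable women per group, which means 124–125 randomised per group with 20% loss. If 110 evaluable was intended, say that it corresponds to about 84% power.
- Show the attrition step as division by 0.8, and state that randomising 264 is expected to leave about 105 evaluable per group and about 82% power.

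Then reconcile the Abstract, the Participants section and Table 1 with the power section, saying for each figure whether it counts women randomised or women evaluable. If 220 is the number randomised, the 80% must be restated as about 75% under 20% loss.

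The cost is a few sentences and the matching figures in three other places. If 264 is confirmed as the number randomised, no additional participants are needed to meet the stated 80%; if it is 220, that cannot be said.
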